## Methods/Design

### Trial design

This is a randomised, parallel-group, two-arm, open-label, single-centre study currently being conducted in an acute psychiatric ward in Japan. It has been approved by the Yokohama City University Medical Research Ethics Committee and registered at ClinicalTrials.gov (registration number: NCT01869660). To avoid biased allocation, randomisation is undertaken by central allocation using a computerized random number generator at the Internet Data and Information Center for Medical Research (INDICE), provided by the University Hospital Medical Information Network (UMIN) in Japan. After written informed consent has been obtained, randomisation is performed to assign patients, in a 1:1 allocation ratio, to either the SDM model intervention or TAU with stratification by sex, age (under or over 20 years old), and assumed duration of illness (less or more than one year) via the minimisation method. Due to the nature of the study, neither the patient nor staff can be blinded. Figure 1 provides an overview of the trial flow. Additional file 1 depicts a summary of the study parts and their timing in the intervention and control groups. We estimate that data gathering will be completed in March 2015.

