### Secondary outcome

These are attitudes toward medication, symptom severity, and treatment continuation. The Japanese version of the Drug Attitude Inventory-10 (DAI-10) [25,26] is used to measure attitudes toward medication. It is a 10-item self-report instrument, with each item being rated as either true or false with regard to the nature of patient experiences with psychotropic drug use. Scores range from -10 to 10, with higher scores indicating a more positive attitude towards medication. The DAI-10 is administered at discharge in the study. The Japanese version of the BPRS, Oxford version, is used to assess symptom severity, which the ward doctor undertakes routinely for all the patients at admission and discharge. Treatment continuation is assessed from their medical records if the patient continues treatment at the Numazu Chuo Hospital and, if not, by asking patients via a telephone call six months post-discharge.

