### Sample size calculation

The primary outcome is the mean difference in treatment satisfaction as measured by the CSQ-8J between the SDM group and the TAU group at the time of discharge from the acute psychiatric ward. In the study by Loh et al. [27], among patients with newly diagnosed depression in primary care settings, the standardised mean difference between a SDM intervention group and a TAU group for the CSQ-8 was 0.92. We expect a smaller effect size of 0.80 because the study population of first-admitted patients with schizophrenia is a potentially more complex problem. Assuming a power of 80% and two-sided significance level of 5%, we estimate that a sample size of 26 patients per arm is required to detect an effect size of 0.80. In order to adjust for loss of power due to an anticipated drop out of 10%, 58 patients will be included.

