### Statistical methods

The data will be analysed on an intention-to-treat principle. Multiple imputation methods [28] will be used for imputing any missing information regarding outcome measures. Unadjusted comparisons of outcome measures between the groups (SDM vs. TAU) will be conducted using Student’s t test or Mann-Whitney U test, depending on the variable distribution for continuous variables (i.e. treatment satisfaction, attitude toward medication, and symptom severity) and chi-squared test for the categorical variable (i.e. treatment continuation). To control characteristics such as sex, age, and duration of illness, we will use a general linear model or a generalised linear model with log-link function, depending on the variable distribution for the continuous variables and a logistic regression model for a categorical variable. Analyses will be performed using R version 3.0.2.

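### Admission BPRS, the only severity baseline described, is not named as a covariate for CSQ-8J or DAI-10; prespecifying it would be a low-priority improvement

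*Protocol article*

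**What the plan says.** The Statistical methods section of the protocol article plans unadjusted comparisons first, using a t test or Mann-Whitney test for the continuous outcomes. Adjusted models follow: "To control characteristics such as sex, age, and duration of illness, we will use a general linear model" or a generalised linear model, depending on the distribution. It does not say which of the two analyses of CSQ-8J is primary.

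The three characteristics named there are the minimisation factors. The Trial design section describes "stratification by sex, age (under or over 20 years old), and assumed duration of illness (less or more than one year". Symptom severity is not one of them.

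Under Secondary outcome, the BPRS is described as an assessment "which the ward doctor undertakes routinely for all the patients at admission and discharge". The same section places DAI-10 at discharge, and the Primary outcome section defines CSQ-8J at discharge. No earlier measurement of either is described.

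The Sample size calculation section states that "a sample size of 26 patients per arm is required to detect an effect size of 0.80" and, allowing for loss, "anticipated drop out of 10%, 58 patients will be included".

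**The concern.** Neither CSQ-8J nor DAI-10 can be adjusted for its own starting value, because none is described. Admission BPRS is then the only clinical severity baseline that the document describes, and it is already recorded for everyone. Severity is balanced neither by the minimisation nor by any covariate that the article names. The entry exclusion for severe conceptual disorganisation caps one BPRS item; it does not balance overall severity between arms.

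Satisfaction and attitude to medication at discharge may plausibly depend on how ill the patient was at admission, although the document does not quantify this. If they do, two things are at stake. In a trial of 58, a chance difference in severity would be carried in part into the estimated treatment difference. Some explainable variance would also stay in the error term. If severity is not prespecified and the arms turn out to differ, the choice is to leave the difference in or to adjust after seeing the data, in an open-label trial with a self-reported primary outcome.

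**Working it through.** **Inputs from the protocol article.** Standardised effect 0.80, power 80%, two-sided 5%, 26 per arm, 10% dropout and 58 in total (Sample size calculation); 1:1 allocation (Trial design).

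**Assumed input.** The correlation r between admission BPRS and the outcome, given sex, age and duration of illness. The document gives no value, so r = 0 to 0.4 is shown.

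**1. The plan's own figure.** For a two-sample t test with n per arm, the noncentrality is 0.80 × √(n/2) on 2n − 2 degrees of freedom.
- The exact solution is n = 25.52, so 26 per arm.
- At n = 26 the noncentrality is 0.80 × √13 = 2.884 on 50 df, and power is 80.7%.
- Dropout: 52 / 0.90 = 57.8, so 58.

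The stated sample size reproduces, and this point does not affect it.

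**2. Power with admission BPRS added, 26 analysed per arm.** The covariate multiplies the residual variance by 1 − r². Estimating its slope multiplies the variance of the treatment difference by (N − 3)/(N − 4) = 49/48, with N = 52. One degree of freedom is lost, leaving 49. The noncentrality is therefore 2.884 × √(48/49) / √(1 − r²).

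| Assumed r | Variance factor (1 − r²) × 49/48 | Power |
|---|---|---|
| BPRS not in model | 1 | 80.7% |
| 0 | 1.021 | 79.9% |
| 0.1 | 1.011 | 80.3% |
| 0.2 | 0.980 | 81.5% |
| 0.3 | 0.929 | 83.5% |
| 0.4 | 0.857 | 86.3% |

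On variance alone, break-even is where 1 − r² = 48/49, so r = 1/7 ≈ 0.14; counting the lost degree of freedom moves it to just under 0.15. The largest loss, at r = 0, is 80.7 − 79.9 = 0.8 percentage points.

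**3. Chance imbalance in severity, 29 per arm.** Without balancing on severity, the standardised difference in admission BPRS between arms has SD √(2/29) = 0.263.
- Above 0.3 SD in either direction: 0.3/0.263 = 1.14, probability about 25%.
- Above 0.5 SD in either direction: 0.5/0.263 = 1.90, probability about 6%.

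With 26 per arm the SD is √(2/26) = 0.277, and the probabilities are about 28% and 7%.

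**4. What an imbalance does to the unadjusted estimate.** The shift is r × imbalance.
- At r = 0.3, a 0.5 SD imbalance shifts the estimate by 0.15 SD, which is 0.15/0.80 = 19% of the planned effect.
- At r = 0.3, a typical imbalance of one SD of its distribution (0.263) shifts it by about 0.08 SD.
- At r = 0 the shift is nil.

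**The case against.** The case against is substantial, and most of it stands.

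- **The list is open.** The covariates are introduced as examples. A reader might infer that admission BPRS has been excluded; the text does not say so. The article condenses a fuller protocol, and an analysis plan not shown may name further covariates. All that can be said is that the article does not name it.
- **The present choice is sound.** Adjusting for the minimisation factors is right. A reader might infer that omitting a prognostic covariate biases the comparison or inflates type I error. It does neither: over randomisations the estimate is unbiased, and its standard error already allows for chance imbalance.
- **The gain rests on an unknown correlation.** BPRS is not the baseline of CSQ-8J or DAI-10, it is rated on admission to a ward with an average stay of 45 days, and the entry exclusion may narrow its range. The document gives no ground for expecting any particular r. Below about 0.14, adjustment costs a little power.
- **The adjusted model may not be primary.** A reader might assume that it is. The article does not say so, lists the unadjusted tests first, and has a sample size that matches an unadjusted t test. If the unadjusted test is primary, a new covariate leaves the primary result unchanged.

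What survives is narrower. The baseline is already collected, severity is not otherwise controlled, and naming it beforehand removes a choice that would otherwise be open once the data are seen. The worst-case loss is small beside the gain at a moderate r.

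**Conclusion.** The point holds as a low-priority improvement. The article states nothing false here, and its sample size and existing adjustment stand.

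The main benefit is protection against chance imbalance: a severity difference above 0.3 SD in about one trial in four, and above 0.5 SD in about one in seventeen (6%), at 29 per arm. How much this matters depends wholly on r; the 0.15 SD shift needs both r = 0.3 and a 0.5 SD imbalance.

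The precision benefit is modest and uncertain: a change in power of −0.8 points at r = 0, +0.8 at r = 0.2, +2.8 at r = 0.3 and +5.6 at r = 0.4. These figures assume 26 analysed per arm, a true effect of 0.80, a linear relation with CSQ-8J, and r taken as the partial correlation given the three named covariates. The same reasoning applies to DAI-10, for which the document states no target effect.

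**What to change.** In the Statistical methods section, or in the analysis plan if it is not already there:

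1. Name the admission BPRS total score as a continuous covariate, alongside sex, age and duration of illness, in the adjusted models for CSQ-8J and DAI-10.
2. Include it in the imputation model for these outcomes.
3. State that this adjusted model is the primary analysis of CSQ-8J. Without this, the change may not reach the primary result.

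This should be settled before outcome data are compared by arm. It takes a sentence or two of text and one degree of freedom, with no new data, visits or patients. The downside is a power loss of under one percentage point if r is below about 0.14.

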### Recruitment

The project supervision team checks the medical records of all patients admitted to the acute ward and nominates candidates for the study within three days after admission. After being verified to satisfy all of the inclusion criteria, the patient is asked to give written informed consent by the investigator (MI). The participant or, if the participant is under 20 years of age, the legal guardian, must provide written informed consent before any study procedures occur.

### Research ethics approval

This study is designed and undertaken in compliance with the Helsinki Declaration and the Guidelines on Clinical Research of Japanese Ministry of Health, Labour, and Welfare. The protocol, informed consent forms, and other requested documents, including any subsequent modifications, were reviewed and approved by the Yokohama City University Medical Research Ethics Committee (21/03/2013). The Ethics Committee is monitoring our study and we will withdraw the study immediately on their direction of discontinuation. We will ensure the protection of all participants’ rights during the study. To address the issues associated with obtaining consent from inpatients with schizophrenia who are symptomatic, we exclude individuals who have conceptual disorganisation as measured by the BPRS (rating of five or more). Furthermore, the consent procedure is designed to enhance the intake and retention of information.

## Discussion

This study is the first to evaluate the efficacy of SDM for patients with early-treatment-stage schizophrenia. It is significant that the study targets patients in the early stage of treatment because the effect of psychosocial interventions, such as SDM, would be influenced by past treatment experience and the influence of treatment in the early stages for a long-term outcome is considered strong [12,29]. Another strength of the current study is that the intervention includes both patients and staff. Since SDM is a process based on cooperation between patients and staff, an intervention that includes both sides is needed; however, there were interventions that either focused on the physician’s understanding and communication skills or on informing patients about treatment options [30]. The intervention program in this study is innovative in that it includes the patient and staff who are involved in the treatment, such as the psychiatrist, nurse, social worker, and pharmacist.

There are some difficulties regarding the study design. Performance bias can occur because a blind trial at the intervention level is not possible. The standardised execution of the intervention is another point of concern. To address these issues, a study supervision team that is not involved directly in the treatment observes the protocol and facilitates staff training programs and intervention sessions. Lastly, as the current study is undertaken in a single centre, further research is needed to assess generalizability.

## Abbreviations

SDM: Shared decision making; TAU: Treatment as usual; BPRS: Brief psychiatric rating scale; DAI-10: Drug attitude inventory; CSQ: Client satisfaction questionnaire; INDICE: Internet data and information center for medical research; UMIN: University hospital medical information network.
